### RANDOMIZATION:

Randomization to XXK capsule or CDS tablet will be in a 1:1 ratio

---

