### **3.2 Sample size**

#### **Initial estimation of sample size**

Since this trial adopts an adaptive design, we initially estimated the sample size based on one of the primary efficacy endpoints, i.e. the proportions of patients who were angina-free according to findings from other and previous studies[1-2]. We assume that the effective rate in the proportions of patients who were angina-free of the trial group was 30%, while that of the control group was 20%. We chose a significance level of 0.05 and a target test power of 0.80. The trial is planned to enroll 465 patients. Considering the dropout rate and stratified block based on the site, the sample size is enlarged to 576 and one planned interim analyses by a Data Monitoring Committee (DMC) will be performed after 288 patients enrolled. Enrollment will be suspended if XXK capsule is found to be significantly more efficacious than the CDS tablets and the O’Brien–Fleming spending function according to the method of Lan and Demets will be applied.

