#### ***Sample size re-estimation***

***In the interim analysis (288 patients enrolled), according to the previous accumulative data in this trial, the proportions of patients who were angina-free***

*between the two groups can not reach the statistical power. The proportions in angina-free of the trial group was 29.17%, while that of the control group was 20.99%. Therefore, the sample size was expanded to enroll 736 patients considering a low dropout rate.*

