#### **11.2 Dynamic statistical plan**

One interim analyses will be conducted under blinding conditions after 1/2 of the total number of cases have completed the trial.

Statisticians and principal investigators are responsible for drafting a written plan for statistical analysis according to the study protocol. It includes the number of included, excluded or withdrawal patients, the demographic and baseline characteristics of included patients, treatment compliance, efficacy analysis and safety analysis.

Qualitative data will be described with absolute and relative (proportion or percentage) values; and quantitative data will be summarized with mean, standard deviation, maximum, minimum, and median.

Paired t-test will be used for comparison before and after treatment within a treatment group. In analysis of variance (ANOVA) for multiple comparisons within a group, if the variances are assumed to be equal, then Student-Newman-Keuls (SNK) significance test will be used for pairwise comparison; if the variances are not assumed to be equal, then non-parametric test will be applied. Two-samples t-test will be used for comparison between treatment groups. Fourfold table will be displayed for comparison of categorical parameters: Chi-squared test for nominal categorical data and rank sum test for ordinal categorical data. Also, the analysis of covariance (ANCOVA) can be used to control for potential confounding variables.

All *P* values are two-side. Statistical significant level is set to be 0.05.

For between-group comparisons, chi-square test, Fisher's exact test, Wilcoxon rank test or Cochran-Mantel-Haenszel (CMH)  $\chi^2$  test may be used for qualitative data; while t-test, ANOVA, Wilcoxon rank test or ANCOVA may be applied for quantitative data.

**Baseline analysis:** Demographic and baseline characteristics will be reported for each subject. Comparisons between the treatment groups will be conducted using ANOVA or

Chi-square test to assess the degree to which comparability of randomization can be achieved.

**Dropout analysis:** The overall dropout rate and the dropout rate due to AEs will be compared between the treatment groups by using Chi-square test.

**Efficacy analysis:** The effect of different study sites on efficacy parameters will be considered and analyzed.

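### The 465 patients in section 3.2 give about 70% power, not 80%, under the two-sided 0.05 test that section 11.2 prescribes

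*Protocol*

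**What the plan says.** Protocol section 3.2 (initial estimation) bases the size on one of the two primary endpoints, the proportion of angina-free patients. It assumes that the rate for "angina-free of the trial group was 30%, while that of the control group was 20" percent. It then says "We chose a significance level of 0.05 and a target test power of 0.80. The trial is planned to enroll 465 patients". It does not say whether the 0.05 is one-sided or two-sided. The 465 is enlarged to 576 for dropout and for site-stratified blocks, with no dropout rate given.

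The synopsis fixes the allocation: "Randomization to XXK capsule or CDS tablet will be in a 1:1 ratio". Section 11.2 fixes the sidedness of the analysis. Of all P values it says that they are two-sided and at what level: "values are two-side. Statistical significant level is set to be 0.05". The protocol mentions no one-sided test.

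After the interim analysis, section 3.2 (re-estimation) reports angina-free rates of 29.17% and 20.99% and concludes: "Therefore, the sample size was expanded to enroll 736 patients considering a low dropout rate". It gives no significance level, sidedness, power target or dropout figure for that step.

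**The concern.** Rates, level, power and size are all stated in section 3.2, and the sidedness of the test is stated in section 11.2. Together they over-determine the calculation, so they can be checked, and they disagree. The question is not left open for a statistical analysis plan, because the protocol itself fixes every input.

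At stake is what a non-significant result on this primary endpoint would mean. Someone relying on section 3.2 would take the risk of missing a true difference of 30% versus 20% to be 20% with 465 evaluable patients. Under the test that will be used it is about 30%. The re-estimation invites the same misreading, since it was made because the interim comparison was judged short of power.

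**Working it through.** **Inputs.** Rates 0.30 and 0.20, level 0.05, power 0.80, total 465 and enlarged total 576 (section 3.2, initial estimation). Interim rates 0.2917 and 0.2099, and total 736 (section 3.2, re-estimation). Allocation 1:1 (synopsis). Two-sided test at 0.05 (section 11.2). The 465 is read as evaluable patients, because dropout is added afterwards.

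**Formula** (pooled variance under the null, 1:1), with p̄ the mean of the two rates and d their difference:

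n per arm = [z_α·√(2p̄(1−p̄)) + z_β·√(p₁(1−p₁)+p₂(1−p₂))]² / d²

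For 0.30 versus 0.20: p̄ = 0.25, √0.375 = 0.6124, √0.37 = 0.6083, d = 0.10.

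**Reproducing 465.**
- One-sided 0.05, 80% power: (1.645×0.6124 + 0.842×0.6083)²/0.01 = 230.8 per arm, 461.6 in total.
- Two-sided 0.05, 70% power: (1.960×0.6124 + 0.524×0.6083)²/0.01 = 230.8 per arm, 461.6 in total.

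Both come within 1% of 465, so the figure does not show which was done.

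**The calculation as stated, two-sided 0.05 and 80% power.** (1.960×0.6124 + 0.842×0.6083)²/0.01 = 293.15 per arm, 586.3 in total (588 if each arm is rounded up). Other two-sided variants give 581 (unpooled), 583 (arcsine), 589 (averaged rate) and 626 (continuity-corrected). None is near 465.

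**Power of the stated sizes**, from Φ{[d√n − 1.960·√(2p̄(1−p̄))] / √(p₁(1−p₁)+p₂(1−p₂))}:
- 465 (n = 232.5): (1.5248 − 1.2002)/0.6083 = 0.534, power 70.3%.
- 576 (n = 288), no dropout: (1.6971 − 1.2002)/0.6083 = 0.817, power 79.3%.
- 736 (n = 368), no dropout: (1.9183 − 1.2002)/0.6083 = 1.181, power 88.1%.

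Summing over the binomial distributions of the chi-square test gives 70.5% for 465 and 79.5% for 576, so the approximation is sound. The step from 465 to 576 implies an allowance of 1 − 465/576 = 19.3%. If that loss occurred, power would return to about 70%.

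**Interim look.** With an assumed final two-sided level of 0.049, power at 465 is 70.0%. The single O'Brien–Fleming look therefore does not explain the gap, and it would raise the required size, not lower it.

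**Re-estimate.** At 0.2917 versus 0.2099: p̄ = 0.2508, √0.3758 = 0.6130, √0.3725 = 0.6103, d = 0.0818.
- Two-sided 0.05, 80% power: (1.960×0.6130 + 0.842×0.6103)²/0.0818² = 439.6 per arm, about 880 in total before dropout.
- Two-sided power of 736, no dropout: (1.5692 − 1.2015)/0.6103 = 0.602, power 72.7%.
- With 692 evaluable (assumed 6% dropout): (1.5216 − 1.2015)/0.6103 = 0.524, power 70.0%.

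**Two-sided power of 736 by assumed dropout.** The protocol gives no rate, so these are assumptions.

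| Assumed dropout | 30% vs 20% | 29.17% vs 20.99% |
|---|---|---|
| 0% | 88.1% | 72.7% |
| 6% | 86.1% | 70.0% |
| 10% | 84.6% | 68.1% |

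**The case against.** The strongest reply is that 465 was never the final enrolment target. It became 576 and then 736, and the only effect for which section 3.2 states 80% power is 30% versus 20%. At that effect 736 gives about 88% two-sided, and about 85% even with an assumed 10% dropout. This stands: the amended trial exceeds its target at its own design effect. A reader might infer that the trial as amended has only 70–73% power. That merges two different cases, 465 patients at the design rates and 736 at the interim rates, and the documents do not support it as a general statement.

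A reader might also infer that the sponsor used a one-sided test. The protocol does not say so, and the number cannot distinguish a one-sided level at 80% power from a two-sided level at 70% power. The consequence for the two-sided test is the same either way.

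For the re-estimate, it is fair to object that section 3.2 restates neither level, power nor dropout. A one-sided calculation at the interim rates gives about 692, and 736 then implies 1 − 692/736 = 6.0% dropout. But that 6% is solved backwards from 736, so the match confirms nothing. What remains is conditional: if the 0.80 target carries over, 736 is below the roughly 880 required before any dropout.

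The reply does not rescue 465. The enlargement to 576 was made for dropout and site blocks, and even with no loss it leaves power just under 80%.

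**Conclusion.** The point holds. The size and power stated in section 3.2 are not what the two-sided test of section 11.2 delivers: about 586 evaluable patients are needed where 465 are stated, and 465 gives about 70% power instead of 80%. This rests on the stated rates, 1:1 allocation, a two-sided 0.05 test, and reading 465 as evaluable patients. It does not depend on the choice of formula.

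The point about 736 is secondary and rests on the 0.80 target carrying over. At the interim rates 736 gives about 73% with no dropout and about 70% with an assumed 6%.

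A reader might want to quote conditional power at 736 as well. The documents do not support a figure, because the interim denominators are not given. An even split of 288 would be 144 per arm; 42/144 gives 29.17%, but 30/144 is 20.83% and 31/144 is 21.53%, so no count out of 144 gives 20.99%.

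Type I error, the test and the effect estimate are untouched, and enrolment has already been raised. The passage should be corrected, but the error does not undermine the trial.

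**What to change.** In section 3.2, state that the calculation refers to the two-sided 0.05 test of section 11.2. Correct the evaluable size for 80% power at 30% versus 20% to about 586, and note that 465 gives about 70%. For the amended size, state that 736 gives about 88% at 30% versus 20% and about 73% at 29.17% versus 20.99% with no dropout. Name the dropout rate actually assumed and give the corresponding figures (for example about 86% and 70% if it is 6%). Do not add a conditional power figure.

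The cost is a change of protocol wording. No extra patients are needed. The downside for the sponsor is a less favourable stated power for the initial size and at the interim effect.

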#### ***Sample size re-estimation***

***In the interim analysis (288 patients enrolled), according to the previous accumulative data in this trial, the proportions of patients who were angina-free***

*between the two groups can not reach the statistical power. The proportions in angina-free of the trial group was 29.17%, while that of the control group was 20.99%. Therefore, the sample size was expanded to enroll 736 patients considering a low dropout rate.*

### **3.3 Randomization and case assignment**

For the allocation of participants, a computer-generated list of random numbers was used. Randomization sequence was created using SAS 9.1 statistical software and was stratified by study site with a 1:1 allocation using random block sizes of 2, 4, and 4. Study participants will be serially numbered as 001-576 and randomly assigned to receive treatment with XXK capsule or CDS tablets (288 in the trial group and 288 in the control group).

**Case assignment in 4 participating sites**

| Sites                                                                | Trial group | Control group | n   |
|----------------------------------------------------------------------|-------------|---------------|-----|
| The First Hospital Affiliated to Tianjin University of TCM           | 72          | 72            | 144 |
| The Second Hospital Affiliated to Liaoning University of TCM         | 72          | 72            | 144 |
| The TCM Hospital of Xinjiang Uygur Autonomous Region                 | 72          | 72            | 144 |
| The Jilin Provincial Hospital of Integrated TCM and Western Medicine | 72          | 72            | 144 |

#### ***Changes:***

*After the interim analysis, the sample size was re-estimated and expanded to enroll 736 patients. Therefore, 160 cases (numbered as 577-736) were added and randomly assigned to receive XXK capsule or CDS tablets ( 80 in the trial group and 80 in the control group) and the final case assignment in 4 participating sites was:*

| Sites | Trial group | Control group | n |
|-------|-------------|---------------|---|
|-------|-------------|---------------|---|

|                                                                      |           |           |            |
|----------------------------------------------------------------------|-----------|-----------|------------|
| The First Hospital Affiliated to Tianjin University of TCM           | 92 | 92 | 184 |
| The Second Hospital Affiliated to Liaoning University of TCM         | 92 | 92 | 184 |
| The TCM Hospital of Xinjiang Uygur Autonomous Region                 | 92 | 92 | 184 |
| The Jilin Provincial Hospital of Integrated TCM and Western Medicine | 92 | 92 | 184 |

### 3.4 Selection of control group

Based on the comparability principle, Compound Danshen (CDS) tablet is selected as the control group in the trial, whose indications and functions are similar to those of XXK capsule.

### 3.5 Blinding

Since the dosage forms of XXK capsule and CDS tablet are different, dummy preparations in both capsule and tablet forms are prepared to allow for double-blind and double-dummy comparison.

Blinding is conducted in two steps in this trial, i.e. treatment is randomly assigned to patients in the first step, and then A or B is randomly assigned to the treatment in the second step. The randomization lists of the two blinding steps are kept in sealed envelopes in duplicate, one stored at the clinical study office of China Academy of Chinese Medical Sciences and the other kept by the sponsor.

Two-step unblinding will be performed after all patients have completed the trial. Step 1: after all data is locked, personnel who keeps the sealed envelop will assign A or B to either of the treatments for the conduct of statistical analysis and production of statistical reports. Step 2: after the statistical analysis is finished and the clinical trial report is prepared, the corresponding treatment that A or B refers to will be unblinded.

An emergency envelope will also be provided along with each test drug in its package, which should only be opened in case of emergency unblinding.

A patient's treatment assignment should only be unblinded when knowledge of the treatment is essential for the further management of the patient.

If the identity of the test medication is necessary for patient management (in the case of a serious complication or a serious adverse event), emergency unblinding is permitted. Investigator, project manager, and clinical study coordinators should participate in the process of emergency unblinding; when, where and why the unblinding occurs as well as each personnel's signature should also be documented. The principal investigators should make every attempt to contact the sponsor after blinding.

At the time of emergency unblinding, it is also necessary to ensure that adequate procedures are in place to ensure the integrity of the data.

### **3.6 Data Monitoring Committee (DMC) and Implementation & Decision-making Committee**

To ensure the validity and integrity of the trial, two committees are established by the multi-center study coordination committee, i.e. Data Monitoring Committee (DMC) and Implementation & Decision-making Committee. DMC is responsible for ensuring the integrity and accuracy of data collection; and the latter (consists of leaders of each site and principal investigators) is responsible for monitoring the implementation of the trial and making important decisions related with the trial process.

### **3.7 Interim analysis**

One interim analyses will be conducted under blinding conditions after 1/2 of the total number of cases have completed the trial. The statistical results of interim analysis will be reported to the Data and Safety Monitoring Board and Implementation & Decision-making Committee, which will decide the subsequent arrangement and calculate the needed number of cases in the next stage of trial. If one group of treatment is terminated after the interim analysis, patients in this group may choose to crossover to continue with the trial or discontinue treatment and only report their safety information (considered as dropout cases).

## **4. SELECTION AND WITHDRAWAL OF STUDY PARTICIPANTS**

### **4.1 WM (Western Medicine) and TCM diagnostic criteria of angina pectoris**

According to the "Guiding principle of clinical research on novel TCM preparations in the

treatment of angina associated with coronary heart disease”[3], and “Nomenclature and criteria for diagnosis of ischemic heart disease” reported by the Joint International Society and Federation of Cardiology/World Health Organization task force on standardization of clinical nomenclature[4], the diagnostic criteria of angina pectoris are developed as follows:

#### **4.1.1 WM diagnostic criteria of angina pectoris**

*Angina of effort:* Effort angina is characterized by transient episodes of chest pain precipitated by exercise or by other situations resulting in an increased myocardial oxygen demand. The pain usually disappears rapidly with rest or with sublingual nitroglycerin. The stable effort angina has 1 month's duration or more.

#### **4.1.2 TCM diagnostic criteria of angina pectoris (blood stasis syndrome)[3]**

Angina pectoris (blood stasis syndrome) is manifested as fixed and stabbing or gripping chest pain, which radiates to shoulder, back or the medial side of the arm, choking sensation in the chest, palpitation, dark purple lips and tongue, thin and choppy pulse.

- Main symptom: chest pain (stabbing, gripping, fixed, and radiating to shoulder, back or the medial side of the arm);
- Accompanying symptoms: chest distress, palpitation, and dark purple lips;
- Tongue and pulse: dark purple tongue, thin and choppy pulse.

If the main symptom and at least 2 accompanying symptoms are observed, along with the manifestations of tongue and pulse, the diagnosis of angina (blood stasis syndrome) could be established.

The six phenotypes of angina (blood stasis syndrome), including chest pain, choking sensation in the chest, palpitation, dark purple lips, ecchymosis on the tongue and fine-choppy pulse constitutes the phenotypic group of blood stasis syndrome.

#### **4.2 Grading of angina pectoris[5]**

According to the “Canadian Cardiovascular Society (CCS) grading of angina pectoris”, the severity of angina can be graded as follows:

Class I: Ordinary physical activity does not cause angina, such as walking and climbing stairs. Angina with strenuous or rapid or prolonged exertion at work or recreation.

Class II: Slight limitation of ordinary activity. Walking or climbing stairs rapidly, walking

uphill, walking or stair climbing after meals, or in cold, in wind or under emotional stress, or only during the few hours after awakening. Walking more than two blocks on the level and climbing more than one flight of ordinary stairs at a normal pace and in normal conditions.

Class III: Marked limitation of ordinary physical activity. Walking one or two blocks on the level and climbing one flight of stairs in normal conditions and at normal pace.

Class IV: Inability to carry out any physical activity without discomfort; angina may be present at rest.

### **4.3 Quantification score of angina pectoris[3]**

#### **4.3.1 Scoring system**

##### **(1) Attack frequency**

0 point: None;

2 points: 2-6 episodes per week;

4 points: 1-3 episodes per day;

6 points: At least 4 episodes per day.

##### **(2) Duration**

0 point: None;

2 points: Lasting  $\leq 5$  minutes per episode;

4 points: Lasting  $> 5$  minutes but  $< 10$  minutes per episode;

6 points: Lasting  $\geq 10$  minutes per episode.

##### **(3) Pain intensity**

0 point: None;

2 points: Ordinary physical activity does not cause angina, such as walking and climbing stairs. Angina with strenuous or rapid or prolonged exertion at work or recreation;

4 points: Slight limitation of ordinary activity. Walking or climbing stairs rapidly, walking uphill, walking or stair climbing after meals, or in cold, in wind or under emotional stress, or only during the few hours after awakening;

6 points: Marked limitation of ordinary physical activity. Walking one or two blocks on the level and climbing one flight of stairs in normal conditions and at normal pace.

##### **(4) Use of nitroglycerin**

a. *frequency of use of sublingual nitroglycerin*

0 point: None;

1 point: Occasionally needed;

2 points: Needed when attack occurs;

3 points: Frequently needed;

*b. time to remission after sublingual nitroglycerin*

0 point: None;

1 point:  $\leq 3$  minutes;

2 points:  $>3$  minutes but  $\leq 5$  minutes;

3 points:  $>5$  minutes;

*c. dose of sublingual nitroglycerin*

0 point: None;

2 points: 1-4 tablets per week;

4 points: 5-9 tablets per week;

6 points: at least 10 tablets per week.

#### 4.3.2 Severity classification

Mild: angina score  $\leq 9$  points;

Moderate: angina score 10-18 points;

Severe: angina score  $\geq 19$  points.

### 4.4 Quantification score of TCM syndrome (phenotypic group)[3]

#### 4.4.1 Scoring system

(1) Chest pain: stabbing, gripping, and fixed pain, which radiates to shoulder, back or the medial side of the arm

0 points: none;

2 points: relieved with rest, daily activities not being affected;

4 points: relieved with medication, daily activities not being affected after remission;

6 points: frequent attacks, daily activities being affected (e.g. putting on clothes, eating, walking, or even making a bowel movement may induce symptoms).

(2) Choking sensation in the chest

0 point: none;

1 point: mild chest distress occurs occasionally, which may disappear without any

intervention;

2 points: frequent chest distress, sighing respiration at times, but daily activities not being affected;

3 points: persistent chest suffocation and sighing respiration, daily activities being affected.

### (3) Palpitation

0 point: none;

1 point: mild palpitation occurs occasionally, which may disappear without any intervention;

2 points: obvious palpitation occurs sometimes, which may last for a relatively long period, but daily activities can be continued;

3 points: persistent palpitation, which may present even at rest, daily activities being affected.

